#### 8.9.2 Serious adverse events (SAEs)

A serious adverse event is any untoward medical occurrence or effect that

- results in death;
- is life threatening (at the time of the event);
- requires hospitalisation or prolongation of existing inpatients' hospitalisation;
- results in persistent or significant disability or incapacity;
- is a congenital anomaly or birth defect; or
- any other important medical event that did not result in any of the outcomes listed above due to medical or surgical intervention but could have been based upon appropriate judgement by the investigator.

An elective hospital admission will not be considered as a serious adverse event.

All SAEs will be evaluated and recorded if relationship is unknown or if SAE is related to study procedures. The sponsor will report the SAEs through the web portal *ToetsingOnline* to the accredited METC that approved the protocol, within 7 days of first knowledge for SAEs that result in death or are life threatening followed by a period of maximum of 8 days to complete the initial preliminary report. All other SAEs will be reported within a period of maximum 15 days after the sponsor has first knowledge of the serious adverse events.

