#### Safety

- To examine the occurrence of adverse events related to the use of a personalized hemodynamic resuscitation protocol within 48 hours and 7 days.
- To assess the rate of acute kidney injury associated with the use of a personalized hemodynamic resuscitation protocol within 48 hours and 7 days.

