|                                    |                                                                                                                                                                                                                                                                                                                                                                                                                                                                                                  |
|------------------------------------|--------------------------------------------------------------------------------------------------------------------------------------------------------------------------------------------------------------------------------------------------------------------------------------------------------------------------------------------------------------------------------------------------------------------------------------------------------------------------------------------------|
| Acute kidney injury                | 
 
• AKI based on KDIGO criteria within 48 hours
 
• AKI based on KDIGO criteria within 7 days
 
• Change in Serum Creatinine Levels from Baseline to 48 hours
 
• Change in Serum Creatinine Levels from Baseline to day 7 (or hospital discharge, whichever came first)
 
• Requirement for renal replacement therapy (RRT) within 7 days
 
• Requirement for renal replacement therapy (RRT) within 30 days
 
 |
| Major Adverse Cardiac Event (MACE) | Any of the following within 30 days: 
 
• Cardiovascular death
 
• Nonfatal myocardial infarction
 
• Nonfatal stroke
 
                                                                                                                                                                                                                                                                                                               |

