| Vasopressor therapy                | 
 
• Vasopressor therapy within three hours
 
• Vasopressor therapy within 7 days
 
• Time to vasopressor therapy
 
                                                                                                                                                                                                                                                                                                                   |
| All-cause mortality                | 
 
• Mortality within 48 hours
 
• In-hospital mortality
 
• Mortality within 30 days
 
                                                                                                                                                                                                                                                                                                                                               |

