## 8.2 Randomisation, blinding and treatment allocation

Subjects will be randomized to either the treatment or control arm of the study, ideally at the moment the treating physician decides to admit the patient to the ED. This randomization process begins as soon as the patient is registered for the ED, even before their arrival.

The randomization process at ED arrival will be facilitated by the REDCap randomization module within REDCap electronic data capture tools hosted at the UMCG. Initially, a researcher will identify potential study participants who meet the inclusion criteria based on information provided by the treating physician. Each prospective participant will be assigned a pseudo-anonymized screening ID generated within the REDCap application. This screening ID will encompass both the deferred consent process and the randomization procedure. The randomization will occur through the REDcap module during the screening, determining the assigned treatment arm.

Once the patient arrives and is included in the study, the assigned treatment arm will be communicated to both the research and treatment teams. Any patients that are enrolled but are found to be ineligible based on exclusion criteria will be exited from the study at that point.

Subjects will be randomized in a 1:1 allocation ratio (treatment to control). It is important to note that the randomization process is not blinded in this study. Both the investigator and the physician are aware of the treatment strategy assigned to each subject.

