### 8.9 AEs, SAEs and SUSARs

#### 8.9.1 Adverse events (AEs)

Adverse events are defined as any undesirable experience occurring to a subject during the study, whether or not considered related to the intervention procedure. All adverse events reported spontaneously by the subject or observed by the investigator or his staff will be recorded.

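### Section 8.9.2 records SAEs only if related or of unknown relation, contradicting the all-AE rule in 8.9.1 and making the SAE tally depend on open-label causality judgement

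*Protocol*

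**What the plan says.** Section 8.9.1 of the protocol defines an adverse event as any undesirable experience during the study, "whether or not considered related to the intervention procedure". It continues: "All adverse events reported spontaneously by the subject or observed by the investigator or his staff will be recorded".

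Section 8.9.2 defines serious events by the usual outcome criteria and then states: "All SAEs will be evaluated and recorded if relationship is unknown or if SAE is related to study procedures". The next sentence moves on to the ethics committee: "The sponsor will report the SAEs through the web portal". It sets the reporting deadlines and adds no relatedness limit of its own.

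Section 8.2 describes an unblinded trial: "Both the investigator and the physician are aware of the treatment strategy assigned to each subject".

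Section 2 lists, among the safety objectives: "To examine the occurrence of adverse events related to the use of a personalized hemodynamic resuscitation protocol within 48 hours and 7 days". Section 8.1.2 lists the safety endpoints separately, for example "AKI based on KDIGO criteria within 7 days" and, under all-cause mortality, "Mortality within 30 days".

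**The concern.** A relatedness condition usually governs what is sent on to an ethics committee and how fast. Here it governs what is written down. A minor unrelated event must be recorded under 8.9.1, while an unrelated life-threatening event need not be recorded as an SAE under 8.9.2.

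The condition is also unlikely to act in the same way in both arms. The causality judgement is made with the allocation known, and the monitor-guided algorithm, the main study procedure an event could be attributed to, exists only in the intervention arm. In infected, unstable patients an event can plausibly be put down to the infection or to the resuscitation strategy. At stake is whether the trial ends with a complete SAE count per arm or with a count that reflects opinion about cause. An analysis plan cannot repair this later, because it cannot analyse SAEs that were never recorded as such.

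**Working it through.** **Step 1. The two rules side by side.**

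| Event | Recorded under 8.9.1? | Recorded under 8.9.2? |
|---|---|---|
| Non-serious, unrelated | Yes | Does not apply |
| Non-serious, related | Yes | Does not apply |
| Serious, related or relation unknown | Yes, as an AE | Yes, as an SAE |
| Serious, judged unrelated | Yes, as an AE | No |

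The conflict is in the last row. An SAE meets the AE definition, so one section requires a record and the other does not.

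**Step 2. Who makes the judgement.** By 8.2, both the investigator and the physician know the arm. By 5.1, control treatment is left to the physician and hospital standards, while the intervention arm follows the stroke-volume algorithm. Controls do have some study procedures: an initial bolus (section 3), and scheduled vital signs and lactate and a fluid ceiling (5.1). The asymmetry is therefore plausible but partial.

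**Step 3. What passes through the filter.** The SAE tally does. The adverse-event objective in section 2 is limited to related events by its own wording, so it rests on the same kind of judgement. The endpoints in 8.1.2 (kidney injury, renal replacement, ventilation or ECMO, cardiac events, vasopressor use, mortality) carry no relatedness condition. Table 1 in 8.3 schedules mortality, organ support, laboratory values and vasopressor data without distinguishing arms. Decompensated heart failure uses physician judgement, but through its own definition and not through 8.9.2.

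**Step 4. Size.** The protocol has no figure to reproduce here: it states neither an SAE rate nor a share judged related. The only input from the document is 94 patients per arm (4.4). The rest is assumption, shown as a range.

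Let *p* be the true risk that a patient has an SAE, equal in both arms, and *r* the share judged related or unknown. Expected recorded patients per arm = 94 × *p* × *r*; for example, 94 × 0.20 × 0.50 = 9.4. The figure after each pair is the probability that a two-sided Fisher test gives p < 0.05 although the true risks are equal.

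| Share recorded, guided / control | *p* = 10% | *p* = 20% | *p* = 30% |
|---|---|---|---|
| 100% / 100% | 9.4 v 9.4; 0.028 | 18.8 v 18.8; 0.034 | 28.2 v 28.2; 0.034 |
| 30% / 30% | 2.8 v 2.8; 0.010 | 5.6 v 5.6; 0.023 | 8.5 v 8.5; 0.027 |
| 30% / 10% | 2.8 v 0.9; 0.028 | 5.6 v 1.9; 0.153 | 8.5 v 2.8; 0.298 |
| 50% / 20% | 4.7 v 1.9; 0.084 | 9.4 v 3.8; 0.267 | 14.1 v 5.6; 0.435 |
| 50% / 10% | 4.7 v 0.9; 0.168 | 9.4 v 1.9; 0.546 | 14.1 v 2.8; 0.794 |

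With equal shares there is no false difference, but at 30% recorded, 1 − 0.30 = 70% of SAEs are missing from the tally.

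The filter can also hide a difference. Assume true risks of 30% guided and 20% control, hence 28.2 and 18.8 patients, and shares of 20% and 30%. Recorded counts are 28.2 × 0.20 = 5.64 and 18.8 × 0.30 = 5.64, so a real excess disappears. Depending on the assumptions, the result is nothing, a spurious excess, or a masked one.

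**The case against.** The strongest reply has four parts.

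- **The planned safety endpoints are untouched.** A reader might infer that the trial's whole between-arm safety comparison depends on unblinded judgement. The protocol does not support that. The endpoints in 8.1.2 are defined without reference to relatedness, and deaths are captured as mortality whatever 8.9.2 says. This part stands in full.
- **No between-arm SAE analysis is stated.** The adverse-event objective concerns related events only, and the statistical section describes no SAE comparison. This also stands. What is exposed is the SAE tally and any comparison someone builds on it.
- **The events may not be lost.** An unrelated SAE is still recordable as an AE under 8.9.1, and the disputed sentence sits among the reporting rules, so a limit on reporting may have been intended. That is possible, and it means one cannot claim that such events vanish. But the sentence governs recording, and the reporting sentence after it carries no limit. Staff following 8.9.2 as written would not enter the event as an SAE.
- **Likely harms are seen elsewhere.** A reader might infer that hypotension after withheld fluid would be hidden by being attributed to sepsis. Vital signs at least twice an hour, the haemodynamic stability endpoints and the vasopressor data cover this in both arms. Events of unknown relation are also kept. That example does not support the point. Serious events outside the listed endpoints, such as limb or gut ischaemia, are where the filter matters.

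**Conclusion.** The contradiction between 8.9.1 and 8.9.2 is plain in the text and should be corrected. If 8.9.2 is followed literally, the SAE tally is selected by causality judgement made with the arm known, and so is any AE or SAE comparison based on it. The conclusion goes no further: the separately defined safety endpoints stand, and neither a false excess nor a hidden one is shown. Size and direction cannot be given, because the protocol states no SAE rate and no relatedness share. The table of false-difference probabilities, running from 0.010 to 0.794, rests wholly on assumed risks and shares and on at most one counted SAE per patient. It shows only that the effect can be negligible or large.

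**What to change.** Amend 8.9.2 so that:

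- all SAEs are recorded in both arms regardless of relation, over the study's existing follow-up (the consent section limits data collection to at most 30 days from ED arrival);
- the causality judgement is a separate field on the SAE record and not a condition for having one;
- any relatedness limit applies only to reporting to the ethics committee, and says so;
- all-cause SAEs are tabulated by allocated arm, beside those judged related.

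This brings 8.9.2 into line with 8.9.1 and lets the related-only count be read against a complete one. The reporting deadlines can stay as they are, and no treatment rule changes. The cost is a little extra data entry for 188 patients, many of whose serious events are already collected as endpoints.

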#### 8.9.3 Suspected unexpected serious adverse reactions (SUSARs)

Not applicable.

### 8.10 Annual safety report

Not applicable.

**8.11 Follow-up of adverse events**

All AEs will be followed until they have abated, or until a stable situation has been reached. Depending on the event, follow up may require additional tests or medical procedures as indicated, and/or referral to the general physician or a medical specialist. SAEs need to be reported till end of study within the Netherlands, as defined in the protocol.

**8.12 Data Safety Monitoring Board (DSMB) / Safety Committee**

Not applicable.

Copy

## 9. STATISTICAL ANALYSIS

All collected data will be stored in the REDcap, and a complete dataset will be uploaded into R version 1.4.1106 using RStudio (2015, RStudio Team, Boston, MA, United States) for further descriptive and statistical analysis. The main analysis will be conducted based on the intention-to-treat (ITT) principle. Descriptive statistics, such as mean, median, standard deviation, and confidence intervals, will be reported for continuous variables. Categorical variables will be summarized using frequencies and percentages.

The ITT analysis will include all subjects who have signed the deferred consent (DC), met the study eligibility criteria, and were randomized to either the treatment or control arm of the study. The ITT population will be the primary and secondary analysis population for this study.

Depending on the changes in treatment arms and protocol violations, we will conduct both a per protocol (PP) sensitivity analysis and a modified intention-to-treat (mITT) analysis. These analyses will be performed to assess the robustness of the study's findings and account for variations in treatment adherence and protocol deviations.

The per protocol analysis will include only the subjects who strictly adherent to the study protocol, completed the assigned treatment as planned, and did not have any major protocol violations. The mITT analysis will include subjects who met the eligibility criteria, were randomized, and received at least one part of the allocated treatment, such as one fluid bolus based on a fluid responsiveness measurement. Unlike in the ITT analysis, participants who were randomized but did not receive any treatment will be excluded from the mITT analysis.

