#### 11.2.1. Recruitment and consent method

1. Upon ED admission, one of the researchers identifies potential study participants meeting the inclusion criteria by information provided by the treating physician. If possible, the patient and/or his/her designated proxy is informed about the study by the researcher, and their consent is sought. If a patient and/or his/her designated proxy does not orally refuse to participate, the patient will be recruited for the study.
2. Once recruited, the patient is randomized according to the study protocol and informed about the randomization results. Following randomization, treatment is promptly initiated as per protocol.
3. The patient themselves and/or his/her designated proxy will be asked to provide deferred consent (DC) within 30 days of the study start. Information about the study will be provided as soon as possible after study entry, which may be at the ED, ICU, or general ward in hospital. If the subject regains mental competence and is capable, their deferred consent for the continuation of their participation in the study must be obtained without undue delay. In cases where the patient is discharged from the hospital and no consent have been obtained, they may be contacted up to three times, and a letter is mailed to obtain deferred consent. Data collection is carried out for a maximum of 30 days from the time of ED arrival. All contact moments will be registered in REDcap' screening field of 'deferred consent'.
4. If the subject does not provide deferred consent, they must be actively informed of the deletion of data previously collected in the study. Throughout the study, participants who signed deferred consent retain the right to withdraw at any time. However, by signing deferred consent, they grant permission to use their collected data for research purposes up to the point of withdrawal.
5. In accordance with the CCMO guidelines on 'deferred consent' in emergency research situations, if a patient passes away before deferred consent is obtained within the 30-day limit, consent for data use is assumed and not sought from legal representatives due to the following reasons:
  - a. Relatives do not have an independent right to review or assess therapeutic or research data as they are no longer legal representatives.
  - b. The patient's wishes cannot be formally established post-mortem, and relatives no longer have a formal role as representatives in the research context.

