  - c. The research under 'deferred consent' has been approved by an ethics committee, prioritizing patient benefits over risks.
  - d. Using data from deceased participants can enhance the reliability of research outcomes, benefiting society and future patients.
  - e. Ethical considerations and transparency require informing relatives about data usage, but their objections may not necessarily lead to data exclusion, depending on the circumstances.

- f. If, however, the deceased patient objects against research through a registration in the UMCG Objection Registry, than further data collected will be halted immediately and data that is collected thus far will be destroyed.
6. The CCMO guideline emphasizes that, from a transparency and ethical standpoint, it is reasonable to inform the patients' family about their study participation in the event of their passing. This communication is important for both providing closure for the family and the completion of the study. Families will be notified through a letter that includes a brief summary of the study and their family member's participation. Contact information is included in the letter.

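### The ITT set requires a signed deferred consent, so patients who die before anyone signs are dropped although section 11.2.1 item 5 allows their data to be used

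*Protocol*

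**What the plan says.** Protocol section 9 (Statistical analysis) sets three conditions for the main analysis set: "The ITT analysis will include all subjects who have signed the deferred consent (DC), met the study eligibility criteria, and were randomized". It continues: "The ITT population will be the primary and secondary analysis population for this study".

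The consent procedure is in section 11.2.1, printed inside section 10.2. Item 3 gives the window and says who may sign: "The patient themselves and/or his/her designated proxy will be asked to provide deferred consent (DC) within 30 days of the study start". Item 5 covers patients who die before that has happened: "consent for data use is assumed and not sought from legal representatives". One of the reasons given is: "Using data from deceased participants can enhance the reliability of research outcomes". The stated exception is an objection recorded in the hospital's registry, which leads to destruction of the data. Item 4 provides for deletion when a subject does not give deferred consent.

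Section 9 also defines a modified set without any consent condition: "The mITT analysis will include subjects who met the eligibility criteria, were randomized, and received at least one part of the allocated treatment".

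Section 8.1.2 lists mortality within 48 hours, in hospital and within 30 days among the secondary endpoints (under safety), and cardiovascular death as a component of MACE within 30 days.

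**The concern.** A patient who dies before consent is obtained has no signature, and under item 5 none will be sought. The consent procedure keeps that patient's data, while the ITT definition excludes the patient. Death is then both the event to be counted and the reason for not counting it.

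The setting makes such cases plausible. Section 10.3 enrols incapacitated patients, including those with septic shock. The window for consent is 30 days, and Table 1 places deferred consent in the 30-day column. The trial is open (section 8.2), so the timing of consent could also differ between arms.

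What is at stake is the validity of the mortality endpoints, and of MACE through cardiovascular death, in the set that section 9 names for the main analysis.

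**Working it through.** **1. The provisions side by side**

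- Section 9: ITT = signed deferred consent, and eligible, and randomised.
- Section 11.2.1 item 5: died before deferred consent = data usable, no signature sought.
- Nothing in the protocol says that assumed consent counts as signed. These patients therefore fail the first condition.
- The mITT set has no signature condition, so a treated patient who died unsigned would be in the mITT set and outside the ITT set. Yet section 9 presents mITT as the set that leaves out further patients (those randomised but untreated).
- Section 9.2 leaves only the binary and time-to-event methods to a later plan. The population is fixed in the protocol itself.

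**2. Effect on an observed mortality proportion**

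The protocol gives no figure for this, so these are scenarios. Inputs: N = 188 randomised (section 4.4); mortality m = 10%, the background in-hospital rate for sepsis quoted in section 1; unsigned share of deaths f, assumed, from 25% to 75%.

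Deaths D = N × m = 188 × 0.10 = 18.8. Dropped = f × D. Observed mortality = (D − fD) / (N − fD).

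| f | Dropped | Left in set | Deaths left | Observed mortality |
|---|---|---|---|---|
| 25% | 4.7 | 183.3 | 14.1 | 7.7% |
| 50% | 9.4 | 178.6 | 9.4 | 5.3% |
| 75% | 14.1 | 173.9 | 4.7 | 2.7% |

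N cancels: observed mortality = m(1 − f) / (1 − mf). It is below m for any f above zero.

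**3. Effect on the arm difference** (all rates assumed)

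- Same unsigned share in both arms, f = 50%, true mortality 10% against 15%: 0.05/0.95 = 5.3% and 0.075/0.925 = 8.1%. A true difference of 5 points appears as 2.8.
- Same true mortality of 10%, but f = 25% in one arm and 75% in the other: 7.7% and 2.7%. A difference of 5.0 points appears where there is none.

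**4. Effect on the primary endpoint**

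The planned size reproduces first. With 0.65 (SD 2.85) against 2.02 (SD 3.44) L, the difference is 1.37 L. The standard error at 85 per arm is √((2.85² + 3.44²)/85) = √(19.956/85) = 0.485. Two-sided Welch power at 0.05 is 0.803 by the noncentral t and 0.800 by simulation with 50,000 replicates, as the protocol states. At 94 per arm simulation gives 0.843.

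With the reduced sets of step 2 and no other loss, power by normal approximation is 0.835, 0.826 and 0.816. It is still 0.805 if every death at 10% mortality were unsigned (169.2 patients left). So the loss of power is small. This uses the protocol's own planning inputs, which come from a 72-hour fluid balance, and says nothing about whether they suit a three-hour volume.

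**The case against.** The best defence is that section 9 is loosely drafted and does not express an intention to exclude. The purpose stated for assumed consent is to use the data of the deceased, and mortality endpoints make little sense otherwise. That is a fair reading of intent. However, an analyst who follows section 9 as written drops these patients, and a later plan that kept them would contradict the protocol.

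The other limits stand, and they rule out several stronger readings that a reader might infer.

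- *All deaths leave the main analysis.* Not supported. A patient or proxy may sign, and item 3 has information given as soon as possible after entry, with 30 days as the outer limit. Patients who sign, or whose proxy signs, and who die later stay in.
- *The primary result is seriously biased.* Not shown. Fluid volume at three hours is mostly observed before death. What remains is selective loss of some of the sickest patients. Effects on ICU admission or renal replacement therapy could be argued in the same way, but nothing in the protocol sizes them.
- *The 40% rate in section 1 gives a fair upper bound.* It refers to septic shock. Entry under section 4.2 needs only one resuscitation criterion, such as a shock index above 0.9, and section 12.1 describes the patients' condition as not immediately life-threatening. Even the 10% is a background figure.
- *Mortality at 48 hours could hardly be measured.* Early deaths are the likeliest to be unsigned, but the protocol has no figure from which to conclude this.
- *The cure is to analyse everyone randomised.* That would bring back patients found ineligible after randomisation, whom section 8.2 exits from the study. It would also bring in living patients who never give consent, whose data item 4 has deleted.

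**Conclusion.** Section 9 is wrong as written. It contradicts section 11.2.1 item 5 and excludes from the primary and secondary analysis population patients whose data the consent procedure keeps. The excluded group is confined to deaths before any signature by patient or proxy. For them the exclusion depends on an outcome, so the three mortality endpoints, and cardiovascular death in MACE, are biased downward, and arm differences can shrink or be distorted.

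The size cannot be fixed from the protocol. At an illustrative 10% mortality, the observed figure would be 7.7%, 5.3% or 2.7% if 25%, 50% or 75% of deaths were unsigned. Both the rate and the shares are assumptions about this trial. The three-hour fluid endpoint is affected only through selective loss of some of the sickest patients. The contradiction itself rests on no assumption and should be removed before the data are analysed.

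**What to change.** In section 9, replace the signature condition of the ITT set with wording such as:

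> have provided deferred consent (patient or proxy), or died before it was obtained and are covered by assumed consent under section 11.2.1 item 5, unless an objection is registered

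In addition:

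- Keep the eligibility condition and analyse patients as allocated.
- Keep the deletion rule of item 4 for living patients who do not provide consent. Section 8.6 words this differently, since it lets the participant decide whether data are retained, so section 9 should say which provision governs.
- Put the same consent condition on the mITT set, so that it cannot contain patients whom the ITT set excludes.
- Report exclusions by arm and reason, including any made after relatives object (item 5e leaves that to the circumstances).

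The cost is one revised sentence and a few lines of reporting. The planned 188 does not change, and for patients who die before consent the procedure in section 11.2.1 already permits use of the data.
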